### Other exploratory outcomes

The pharmacokinetic profile of gestrinone will be characterized in a subgroup of participants (*N* = 15). The pharmacokinetic parameters will be determined: area under the curve (AUC(0-∞)), maximum concentration (Cmax), time until reaching maximum concentration (Tmax), and half-life (t1/2).

### Assessment of outcomes measures

Outcomes measures will be assessed during each of the three study visits in the main study protocol (randomized, double-blind, parallel, placebo-controlled stage), including a baseline visit (pre-treatment), a 3-month visit and 6-month visit. A trained team, including a gynecologist, will conduct the study in the outpatient setting in all study centers. Clinical assessments, monitoring of adverse events, evaluation of androgenization (hirsutism, clitoral index, acne, alopecia, and deepening of the voice), as well as pelvic pain intensity and quality of life assessed by SF-36 questionnaire will be evaluated at all the three study visits. Laboratory blood assessment will be conducted at the baseline visit and in the 3-month visit and include: complete blood count, liver and kidney function (AST, ALT, alkaline phosphatase, urea, creatinine, and uric acid), lipid profile (triglycerides, total cholesterol, HDL, LDL, VLDL) and blood glucose, coagulogram (PT and aPTT), and plasma hormone levels (total testosterone, free testosterone, and SHBG). Quality of life assessment by the EHP-30 questionnaire will be applied at the baseline visit and in the 3-month visit. Data on uterine bleeding pattern and use of medication to relieve pelvic pain will be remotely collected using and electronic diary available at the App used in the study protocol.

Outcomes measures in the EXT-PK (open-label) will be assessed during each of the four study visits in which clinical evaluation, monitoring of adverse events, evaluation of androgenization, pelvic pain intensity and quality of life by SF-36 questionnaire will be conducted in each of the clinical visits, including baseline (pre-treatment), 1-month, 3-month, and 6-month after the insertion of gestrinone subdermal bioabsorbable pellet. Blood sampling for PK study will be conducted: pre-insertion of the gestrinone pellet (predose); different times after insertion of the gestrinone pellet: +24h; 7, 14, 21, 28, 56, 84, 112, 140, 168 days. Data on uterine bleeding pattern and use of medication to relieve pelvic pain will be remotely collected using an electronic diary established to be available at the App established to be used in the study protocol.

### Study procedures

Participant-reported outcomes will be collected *via* the App used in the study protocol: Quality of Life 36-item Form Health Survey (SF-36); endometriosis health profile – Endometriosis Health Profile 30 (EHP-30); diary to record the use of analgesics for pelvic pain and uterine bleeding pattern. On the first visit, access to the App will be provided to the participant; the participant will receive guidance on how to use the App, and baseline data will be collected. Following the study procedure schedule, participants will receive reminders through the App to record outcomes, and telephone contact will be made for those who do not complete the form regularly. At follow-up visits, participants will be retrained if they present difficulties in using it.

## Screening procedures

### Gynecological assessment

A gynecological assessment will be carried out to check the conditions of the female reproductive tract and the suitability for the insertion of the levonorgestrel-releasing intrauterine system (LNG-IUS 12). Furthermore, menstrual history, hormone use, pregnancy, and fertility history will be collected. A transvaginal ultrasound will be performed to assess the positioning of the device.

### Treatments

#### Insertion of the levonorgestrel-releasing intrauterine system (LNG-IUS 12)

The LNG-IUS 12 (Kyleena^®^) must be inserted in an outpatient setting by the investigator following the manufacturer instructions. After carrying out a gynecological examination to check the size and position of the uterus, the cervix should be visualized with the aid of a speculum, and the cervix and the vagina should be cleaned with an antiseptic solution. With the help of the sliding guide, the IUS inserter must be pushed to the bottom of the uterus to position the device.

#### Insertion of the investigational product or subdermal bioabsorbable placebo pellet

The investigator will conduct the procedure in an outpatient setting. After local anesthesia, a small incision (4–5 mm) will be made, through which the pellet will be inserted under the skin of the buttock using a trocar. It will be performed just after the insertion of the LNG-IUS 12, and the randomization procedure.

### Safety and efficacy endpoint assessments

Suspected events and outcomes must be analyzed by the Clinical Events Classification Committee. Safety results should be indicated on the eCRF clinical status page and should be submitted for review.

### Laboratory evaluation

Blood samples (total volume of 10 mL) will be collected through venipuncture from the participant in the following tubes: tubes containing EDTA anticoagulant to perform the blood count, tubes with separating gel (to evaluate biochemical parameters of liver and kidney function, hormonal and lipid profile) or citrate (to perform a coagulogram), observing a prior 8-hour fast. After separating the serum, dosages will be carried out using commercially available kits following the instructions specified by the manufacturer. The local laboratory will conduct the analyses using its protocols and equipment and following Biosafety Standards and Good Laboratory Practices.

## Assessment of androgenization

### Hirsutism

The investigator will assess the degree of hirsutism. The participant should be instructed to suspend hair removal/waxing for approximately 14 days before each visit. The use of lasers for hair removal will not be permitted during the entire study period. To evaluate and quantify hirsutism, the modified Ferriman-Gallwey Scoring System will be used, which includes 9 body regions (excluding the legs and armpits) for access to hair growth, grading from 0 (no terminal hair growth) to 4 (extensive hair growth) in 9 locations. The total score ranges from 0 to 36, with a score greater than 8 considered a sign of androgen excess in Caucasian women. A score of 8 – 15 indicates mild hirsutism; above 15, moderate to severe hirsutism. For other ethnic groups, the amount of hair expected for each specific ethnicity must be considered [22].

### Clitoris measurement

The investigator will measure the participant’s clitoris (portion corresponding to the glans) [23]. The size of the clitoris will be measured using a 15 cm plastic ruler. The Clitoridean Index will be considered as the product of the longitudinal diameter (in millimeters) x transverse diameter (in millimeters), considering clitoromegaly when these measurements are more significant than 6.5 and 4.4 respectively, and the Clitoridean Index greater than 35 mm^2^ [24]. Additionally, the participant’s clitoris corresponding to the part of glans + corpus will be measured and registered.

### Deepening of the voice

A speech therapist will evaluate the participant’s vocal pattern using protocols and equipment validated by evaluating professionals. The participant’s voice will be recorded using a digital recorder for evaluation. The pattern observed on each visit will always be compared with that recorded during the initial visit (Basal) to detect possible vocal changes and, more specifically, the deepening of the voice.

### Assessment of the degree of acne

The severity of acne will be assessed

By using the IGA scale (Investigator’s global assessment) to be used by the trained researcher and described below:0 – Clear skin: no evidence of acne1 – Almost clear skin: some inflammatory lesions and some non-inflamed papules present (developing papules, without redness yet)2 – Moderately severe acne: some non-inflammatory lesions dominate the area with some pustules and papules (there are no cystic lesions)3 – Non-inflammatory acne dominates the area, and some inflammatory lesions can be found. There may or may not be a small cystic lesion in the area,4 – Inflammatory and non-inflammatory acne lesions are more visible. There may or may not be some cystic acne lesions.5 – Severe inflammatory acne dominates the area. Many comedones, pustules, papules, and cystic acne will be present.

## Alopecia

The investigator will assess the occurrence of alopecia according to the presence of rarefaction sequelae on the scalp.

### Uterine bleeding or bleeding-free days

The participant must record in the electronic diary (App) whether there has been uterine bleeding in the last 24 h. If the answer is positive, she must inform us of the intensity of the bleeding (whether spotting or bleeding). Based on the data documented in the participant’s diary, the following parameters will be evaluated:Total number of days of amenorrheaTotal number of bleeding-free days in the reference periodTotal number of days of bleeding and spotting (escape)Total number of days with bleeding or spotting in the reference periodNumber of consecutive bleeding-free daysNumber of consecutive days without bleeding after starting treatmentTotal number of days with spotting (escape)Total number of days with spotting (escape) in the reference periodTotal number of days to cessation of bleeding after starting treatment

The bleeding pattern will be classified according to the criteria of Belsey [25] described below: normal bleeding − 3 to 5 episodes of spotting or bleeding within 90 days; prolonged bleeding – more than 14 days of continuous spotting or bleeding within 90 days; frequent bleeding – more than 14 days of constant spotting or bleeding within 90 days; infrequent bleeding – less than 3 episodes of spotting or bleeding within 90 days; amenorrhea – no bleeding during the 90 days of the reference period.

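### The frequent-bleeding class repeats the prolonged-bleeding rule, so the two cannot be told apart and women with more than 5 short episodes fit no class

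*Protocol article*

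**What the plan says.** The section on uterine bleeding or bleeding-free days first lists nine parameters counted in days from the electronic diary. It then turns to classes: "The bleeding pattern will be classified according to the criteria of Belsey [25] described below". Five follow, each over 90 days. Two rest on a count of episodes: normal is 3 to 5 and infrequent is fewer than 3. A third, amenorrhea, is stated as "no bleeding during the 90 days of the reference period". The remaining two rest on duration. The first of them reads "prolonged bleeding – more than 14 days of continuous spotting or bleeding within 90 days". The second, which comes next in the list and changes only one adjective in the rule, reads "frequent bleeding – more than 14 days of constant spotting or bleeding within 90 days".

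The section gives no order of precedence and does not say whether the classes exclude one another. The diary asks women who report bleeding whether it was spotting or bleeding. Change in bleeding pattern is one of the nine exploratory efficacy endpoints, and bleeding pattern is listed under the other exploratory objectives.

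**The concern.** A class named for frequency should rest on how often bleeding occurs, as normal and infrequent do. Here it rests on the length of one run, and the rule is the one already used for prolonged bleeding. This has two effects. Every woman with prolonged bleeding is also labelled frequent. Women who do bleed often, but briefly each time, have no label. A smaller issue is that infrequent has no lower limit, so a woman with no episodes meets that rule as well as amenorrhea.

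The category table by arm depends on how these points are settled. The article itself names amenorrhea as an effect of gestrinone (mechanism of action; side effects), so a difference between arms in bleeding pattern is plausible. If the rules are settled after the data have been seen by arm, the choice could be influenced by the result.

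**Working it through.** The plan gives no figure to reproduce. The check is whether the five rules, read literally, assign each bleeding history to a class.

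**Inputs**, all from the bleeding section. Let E be the number of spotting or bleeding episodes in 90 days and L the longest continuous run in days.

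| Class | Rule as written |
|---|---|
| Normal | 3 ≤ E ≤ 5 |
| Prolonged | L > 14 |
| Frequent | L > 14 |
| Infrequent | E < 3 |
| Amenorrhea | E = 0 (taking no bleeding to mean no episodes) |

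The adjectives in the prolonged and frequent rules (continuous, constant) are read as synonyms, because the article draws no distinction between them.

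**Grid.** E runs from 0 to 10. For E = 0, L = 0. For each other E, L is 5, 14, 15 or 20 days. That gives 1 + 10 × 4 = 41 combinations.

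| Episodes | L ≤ 14 | L > 14 |
|---|---|---|
| 0 | infrequent + amenorrhea (1 cell) | not possible |
| 1–2 | infrequent (4 cells) | infrequent + prolonged + frequent (4 cells) |
| 3–5 | normal (6 cells) | normal + prolonged + frequent (6 cells) |
| 6–10 | **no class** (10 cells) | prolonged + frequent (10 cells) |

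**Counts**

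- No class: 10 cells.
- Exactly one class: 4 + 6 = 10 cells.
- Two classes: 1 + 10 = 11 cells.
- Three classes: 4 + 6 = 10 cells.
- Total: 10 + 10 + 11 + 10 = 41.

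**Results**

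1. *Duplicate.* Prolonged and frequent occur together in all 4 + 6 + 10 = 20 cells with L > 14, and neither ever occurs alone.
2. *Gap.* With more than 5 episodes and L ≤ 14, none of the 10 cells has a class. With more than 5 episodes and L > 14, a class does apply, but only the duplicated pair.
3. *Overlap at zero.* E = 0 meets two rules.
4. *Spotting only.* Four rules count spotting or bleeding, but amenorrhea is worded as no bleeding. A woman with one or two spotting episodes and no heavier bleeding is infrequent by one rule and might be called amenorrheic by the other.

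These are counts of logical combinations, not expected shares of participants. The article gives no data on how many women would fall in each cell.

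**The case against.** Several objections have force.

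*The endpoint is exploratory.* This is correct. The primary outcome is freedom from serious adverse events and the main secondary outcome is androgenization. Neither uses these classes.

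*Most of the outcome can still be derived.* A reader might infer that the bleeding outcome cannot be derived at all. The text does not support that. The nine day-based parameters do not use the class labels, and normal, infrequent, prolonged and amenorrhea each have a usable rule. Only frequent lacks one of its own.

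*Overlap may be intended.* A duration class can reasonably coexist with an episode class, and nothing says the five are exclusive. That explains a woman who is both normal and prolonged. It does not explain two classes with one rule, or a range of episode counts with none.

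*Zero episodes obviously means amenorrhea.* This is the ordinary reading, and an order of precedence is often left to the analysis plan. The overlap is therefore minor.

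*The cited criteria settle it, and this is only a transcription slip.* It may well be a slip. But the article says the criteria are set out in the text and then sets them out. If the source differs, the article misstates it. The source is not available here, so the point rests only on the text.

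**Conclusion.** The point holds within limits. As written, frequent and prolonged are the same class, and a woman with more than 5 episodes and no run over 14 days has no class. The overlap of infrequent with amenorrhea at zero episodes is real but minor. The effect is confined to the five-class pattern behind one exploratory endpoint.

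A reader might go further and infer that every woman with more than 5 episodes is unclassified. That is false: if any run exceeds 14 days, she falls in the duplicated pair. A reader might also infer harm to the trial's safety conclusions, but no primary or secondary safety outcome depends on this classification. How blank diary days are handled is a separate missing-data matter that can be left to the analysis plan.

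The conclusion rests on reading the two adjectives as synonyms. How many participants are affected is unknown. It should still be corrected, because the stated rule gives a wrong label or none, and the repair is cheap.

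**What to change.** Before the bleeding data are analysed by arm:

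1. Check the five definitions against the cited criteria.
2. Give frequent bleeding its own episode count covering the range above normal. More than 5 episodes per 90 days is the value inferred from the article's limits of 3 to 5 and fewer than 3. The article does not state it, so step 1 should confirm it.
3. Restrict infrequent to 1 to 2 episodes, leaving zero to amenorrhea.
4. State whether women with spotting only count as amenorrheic.
5. Report prolonged bleeding (a continuous run over 14 days) as a separate yes/no flag that may accompany an episode class.

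With these changes, and once step 4 is settled, every episode count falls in one class: 0, 1–2, 3–5 or more than 5.

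The cost is a wording correction and a change to the derivation program. The diary already records bleeding and spotting daily, so no new data are needed.

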### Assessment of changes in the intensity of pelvic pain and dysmenorrhea based on the Visual Analogue scale (VAS/EVA)

The study participants will receive a diagram based on the Visual Analogue Scale shown below to assess chronic non-cyclical pelvic pain and dysmenorrhea. The VAS scale is standardized from 0 (no pain) to 10 (in centimeters) (the worst pain imaginable).

### Record of pre-study and concomitant medications

At the screening visit, pre-study medication use will be recorded. The participant must record in the electronic diary through the App used in the study about the use of concomitant medications, especially for pain relief (analgesics).

### Assessment of patient-reported quality of life

The Medical Outcomes Study 36-item Form Health Survey (SF-36) measured health-related quality of life. Participants must respond to the SF-36 questionnaire. The SF-36 is a multidimensional questionnaire containing 36 items distributed into 8 components: functional capacity, physical aspects, pain, general health status, vitality, social and emotional aspects, and mental health. It has a final score that ranges from 0 to 100, where 0 corresponds to the worst general health status and 100 to the best health status [26].

## Endometriosis health profile 30 (EHP-30)

Participants must respond to the EHP-30 questionnaire. The EHP-30 is a self-report instrument that measures how endometriosis affects a woman’s health status and quality of life. It consists of a central questionnaire composed of 30 items that access 5 dimensions: pain, control and helplessness, emotional well-being, social support, and self-image; and a modular questionnaire with 23 items distributed across 6 scales: sexual relations, work, medical profession, infertility, relationship with children and treatment. Each scale is transformed into a score from 0 to 100, with the lowest score meaning a better quality of life [27].

### Patient satisfaction with treatment

Participants must rate their satisfaction with the treatment by choosing one of the following alternatives presented in written form (ranging from 1 to 5): very satisfied, satisfied, not sure, dissatisfied, or very dissatisfied.

### Pharmacokinetic profile of gestrinone

Blood sampling will be conducted at pre-insertion of the gestrinone pellet; different times after insertion of the gestrinone pellet: +24h; 7, 14, 21, 28, 56, 84, 112, 140, 168 days

A sensitive and specific high performance liquid chromatography-electrospray tandem mass spectrometric (LC-MS/MS) method was developed and validated by a local specialized laboratory for the determination of gestrinone in human serum using nomegestrol acetate-d5 as an internal standard. The limit of quantification (LOQ) was 0.05 ng/mL.

The pharmacokinetic parameters will be evaluated: area under the curve (AUC(0-∞)), maximum concentration (Cmax), time until reaching maximum concentration (Tmax), and half-life (t1/2).

### Reports of pregnancy

Participants should be instructed to notify the investigator immediately if they become pregnant during the study. The investigator must report any pregnancy in study participants that occurs within 30 days of the last administration of the investigational product.

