**Methods:**

One hundred participants with documented deep infiltrative endometriosis who underwent surgery without satisfactory response will be randomly assigned (1:1) to either gestrinone 85 mg subdermal bioabsorbable pellets or placebo. Both arms will receive levonorgestrel-releasing intrauterine system (LNG-IUS 12). The treatment duration will be 6 months, with baseline, 3 months and 6 months clinical visits. The primary endpoint is a combination of serious adverse events (SAEs) accumulated within 6 months of insertion of the gestrinone or placebo pellet and collected through spontaneous reports and clinical findings. They include death, threat or risk to life, need for hospitalization, prolongation of pre-existing hospitalization, permanent disability or damage, congenital anomaly; or significant medical occurrences such as venous thromboembolism. The primary safety outcome will be the percentage of patients who do not experience SAEs 6 months after randomization. Androgenization, changes in laboratory exams and in pelvic pain intensity as well as quality of life (SF-36 and EHP-30 questionnaires) will be further evaluated. Daily data on uterine bleeding patterns and the use of pain relief medication will be remotely collected using an App. Pharmacokinetics profile of gestrinone pellet will be characterized.

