#### Side effects

Most of the adverse effects of gestrinone are due to its androgenic activity and include acne, skin and hair seborrhea, mild hirsutism, edema, weight gain, voice changes, androgenetic alopecia, and clitoral hypertrophy. The drug showed an embryotoxic effect on animals, with a risk of androgenization of female fetuses. It reduces HDL concentrations, and it is recommended to monitor cholesterol and liver transaminase levels in hyperlipidemic patients and glucose levels in diabetic patients. Other effects related to inhibition of the pituitary-ovarian axis may include menstrual disorders and amenorrhea, hot flashes, sweating, breast reduction, changes in libido, vaginal dryness, and emotional fluctuations [13].

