**Figure 2. F0002:**
[figure not shown]
Study design.

Participants eligible for the main stage of the study will be randomized into one of the treatment arms:Experimental: Insertion of the levonorgestrel-releasing intrauterine system (LNG-IUS 12, Kyleena^®^) and gestrinone subdermal bioabsorbable pellet (85 mg)Comparator: Insertion of the levonorgestrel-releasing intrauterine system (LNG-IUS 12, Kyleena^®^) Kyleena^®^ levonorgestrel-releasing intrauterine system and subdermal implant of placebo bioabsorbable pellet

The insertion of the levonorgestrel-releasing intrauterine system (LNG-IUS 12, Kyleena^®^) is necessary as a contraceptive method for all study participants. LNG-IUS (LNG-IUS 12) has been developed for up to 5 years of use with an average release rate of ∼12 μg/24 h over the first year [21]. Clinical assessments will be recorded at recruitment (baseline), 3 and 6 months after pellet insertion. Assessment of the primary outcome will be carried out 6 months after insertion of the gestrinone pellet.

Participants will be invited to an extension phase (open-label) of the study to provide additional long-term safety data (EXT-PK). A subgroup of 15 participants at the end of 6 months of the main stage of the study who accept to participate in the extension phase will receive an insertion of a gestrinone pellet (85 mg), and the serum concentration of gestrinone will be monitored to characterize its pharmacokinetic profile (PK). Clinical assessments will be recorded at recruitment (baseline), 1, 3 and 6 months after pellet insertion. Blood sampling for PK study will be conducted.

Bioabsorbable gestrinone pellets are produced and marketed by Biòs Farmacêutica following standardized procedures and current legislation. Pellets containing a placebo will be prepared under the same conditions as those containing the product ingredient. Biòs Farmacêutica will donate all pellets used in this study.

GLADE is an investigator-initiated project. Biòs Farmacêutica funded the trial but was not involved in the study design, data collection, analysis, interpretation, writing of the manuscript, or decision to publish. The Trial Steering Committee designed the study protocol and is monitoring the trial’s progress. The first draft of the manuscript was written by the first and the last author and revised based on comments from all the authors. No writing assistance was provided.

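### The 30-day pregnancy-reporting window is counted from a single day-0 pellet insertion and, read literally, ends about five months before the treatment and SAE windows close

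*Protocol article*

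**What the plan says.** All references are to the protocol article.

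- **Investigator's duty** (Reports of pregnancy): "The investigator must report any pregnancy in study participants that occurs within 30 days of the last administration of the investigational product".
- **Participant's duty** (same section): "Participants should be instructed to notify the investigator immediately if they become pregnant during the study". This sentence has no 30-day limit.
- **When the product is given.** The section on inserting the pellet describes one insertion and times it thus: "It will be performed just after the insertion of the LNG-IUS 12, and the randomization procedure". No repeat insertion is described for the main stage. Under Study design, a subgroup of 15 who finish the main stage receive one further gestrinone pellet in EXT-PK and are followed for another 6 months.
- **How long treatment lasts** (Abstract, Methods): "The treatment duration will be 6 months, with baseline, 3 months and 6 months clinical visits". Under Primary safety outcome, SAEs are accumulated over 6 months from insertion.
- **How long drug levels are followed after one pellet** (Pharmacokinetic profile of gestrinone): pre-insertion, then at "24h; 7, 14, 21, 28, 56, 84, 112, 140, 168 days".
- **Fetal risk** (Side effects): "The drug showed an embryotoxic effect on animals, with a risk of androgenization of female fetuses".

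**The concern.** A window counted from the last administration works for a drug taken repeatedly, because the last dose falls near the end of exposure. For a pellet inserted once, the last administration is also the first. The clock therefore starts at the beginning of treatment and runs out after one month.

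The investigator's mandatory reporting then stops while the plan still regards the participant as on treatment, is still accumulating her SAEs and, in EXT-PK, is still measuring serum gestrinone. The trial's primary objective is safety, and the article itself states a fetal risk. An on-treatment pregnancy that meets no SAE criterion is the kind of event a dedicated pregnancy rule exists to capture. As written, whether it goes beyond the site after day 30 is left to the investigator.

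**Working it through.** The only figure the plan gives on this point is the 30-day window. It is stated and not derived, so there is nothing to reproduce. The check compares it with the other time spans.

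**Inputs**
- Reporting window: 30 days from last administration (Reports of pregnancy).
- Main-stage administrations: one, on day 0 (pellet insertion section).
- Treatment duration and SAE window: 6 months, taken as 182 days (Abstract, Methods; Primary safety outcome).
- Last scheduled serum gestrinone sample after one pellet: day 168.
- Release duration of the pellet: not stated. This is an assumption, varied below.

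**Main stage, by calendar**
- Inside the rule: 30/182 = 16.5%.
- Outside the rule: (182 − 30)/182 = 152/182 = 83.5%, about 84%.

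**Sensitivity to the unknown exposure time.** If exposure lasts T days after insertion, the share of exposed days outside the rule is 1 − 30/T.

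| T (days) | Inside, 30/T | Outside, 1 − 30/T |
|---|---|---|
| 60 | 50.0% | 50.0% |
| 90 | 33.3% | 66.7% |
| 168 | 17.9% | 82.1% |
| 182 | 16.5% | 83.5% |

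More than half of the exposed time lies outside the rule whenever T exceeds 60 days. These are shares of days. They become shares of conceptions only if conception risk is roughly uniform over the exposure.

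**Including EXT-PK.** Take 50 gestrinone participants in the main stage (half of 100 under 1:1 allocation) and 15 in the extension, each with 180 days of treatment: (50 + 15) × 180 = 11,700 person-days.

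The reading most favourable to the plan treats everything up to 30 days after a participant's final insertion as covered. Let k be the number of the 15 who came from the gestrinone arm. Covered person-days are (50 − k) × 30 + k × 180 + 15 × 30.
- k = 0: 1,500 + 0 + 450 = 1,950, which is 16.7% covered and 83.3% outside.
- k = 15: 1,050 + 2,700 + 450 = 4,200, which is 35.9% covered and 64.1% outside.

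The favourable reading narrows the gap without closing it. In the extension itself, days 31 to 180 stay outside under either reading.

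**The case against.** The strongest reply is that little would be lost in practice.

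- **Participants must notify the site throughout the study.** This stands. Later pregnancies should be known to the investigator, adverse events are assessed at every visit, and any pregnancy complication meeting an SAE criterion is captured for the full 6 months. What lapses is the explicit duty to report onward a pregnancy that is not itself an SAE. A reader might infer that such pregnancies vanish from the trial's records; the text does not support that.
- **Very few pregnancies are expected.** This also stands. Everyone receives an LNG-IUS 12, eligibility excludes women planning pregnancy within 12 months of screening, and the article describes gestrinone as causing anovulation. The point concerns which pregnancies the rule covers and does not predict a count.
- **The release time is unknown.** Correct. A reader might take the 6-month treatment duration and the sampling to day 168 as showing six months of release. They are design choices, and the pharmacokinetic profile is still to be characterized. This is why a range is shown.
- **The last administration may have been meant as the end of the treatment period.** That would close the gap, but the text does not say so, and a pellet inserted once has no later administration.
- **A journal article condenses the protocol.** That would answer a complaint about something absent. Here the article states a specific rule that does not fit its own dosing form. The argument does apply to follow-up of pregnancies to outcome, which may sit in the full protocol and is not raised as a fault.

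A further tempting inference comes from the SAE list in the Abstract: "permanent disability or damage, congenital anomaly; or significant medical occurrences such as venous thromboembolism". Because a pregnancy conceived on study would not normally reach term within 6 months, a reader might conclude that congenital anomaly cannot be observed and should leave the primary outcome. That goes too far. An anomaly can be identified before birth, and it is one criterion in the definition of an SAE, not a separately analysed component. The primary percentage is well defined as it stands.

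**Conclusion.** The point holds as an internal mismatch in safety reporting. The investigator's mandatory window covers the first 30 days after the main-stage insertion, about 16% of a 182-day treatment period, and leaves about 84% of it by days outside. The same mismatch follows the single insertion in EXT-PK.

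The 84% is a calendar share of the treatment period. As a share of exposed time it rests on exposure lasting throughout; shorter assumptions give 82% at 168 days, 67% at 90 and 50% at 60. It should not be quoted as the proportion of exposed conceptions missed, since that also needs a uniform conception risk and disregards the notification duty on participants. The absolute number affected is probably very small. No sample size, test or primary estimate changes. What is at stake is complete reporting of an event that the article's own account of the drug makes important.

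**What to change.** Reconcile Reports of pregnancy with the 6-month treatment and SAE windows. Suggested wording: the investigator reports every pregnancy occurring from pellet insertion through at least the final visit of the stage the participant is in, plus the 30 days already stated. Apply this separately to the main stage and to EXT-PK.

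The first participant was included in February 2023, the last visit was estimated for April 2025, and the article appeared in July 2025. A purely prospective change may therefore come too late. The useful action now is to ask sites for any pregnancy already notified to them in the corrected window and to report those cases with the trial's safety results.

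The cost is one sentence of clarification and one query per site, at 7 sites. The primary outcome definition, including its list of SAE criteria, stays as it is.
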